**Table 2 Tab2:**
[figure not shown]
Schedule of enrollment, intervention, and outcome assessments for VS002A trial

*Screening is expected to be completed on the same single day; stool samples are only collected on D1 and blood samples are collected on D1 and D2 (blood samples for gut health biomarkers are collected for 100 patients); *D=* day; Cholkit test: rapid test for detection of *V. Cholerae*

### Laboratory tests

#### Routine

Blood is obtained by venipuncture to determine serum electrolytes, and blood glucose is determined on admission and 24 h after enrolment. Complete blood count, serum creatinine, stool routine examination, stool bacterial culture, and Rota viral antigen for all patients are done on admission only. Other clinical laboratory investigations, e.g., serum creatinine, blood culture, urine microscopy/culture, stool electrolytes, and chest X-ray, may be performed and repeated if clinically indicated.

#### Gut health markers

In a sub-sample of the first 100 children, plasma vitrulline (CIT) and kynurenine-tryptophan (KT) ratio are measured to have an idea about the changes associated with environmental enteric dysfunction (EED). The tests are done on enrolment and after 24h of the enrollment at icddr,b lab, using the serum collected for routine blood testing, therefore no extra amount of blood or venipuncture is required. Quantitative analyses of plasma CIT concentrations are performed at icddr,b using the enzyme-linked immunosorbent assay (ELISA) method. KT is also be tested at icddr,b using liquid chromatography/quadrupole time-of-flight mass spectrometry (Q-TOF LC-MS) platforms [17].

### Discontinuation procedure

#### Criteria for removal from study and treatment failure

Patients are discharged from the hospital when diarrhea is resolved (the working definition of resolution of diarrhea has been mentioned below). However, no participants are discharged before 24 h from enrolment.If it takes more than 5 days (≥ 120 h) to resolve diarrhea or if a patient becomes dehydrated requiring unscheduled IV fluids, we transfer the patient to the general in- patient’s ward for further evaluation and treatment. In that case, it is considered a “treatment failure.”After enrollment, if any patient develops any co-morbidity like pneumonia, sepsis, electrolyte imbalance or requires specific antibiotics and/or special attention/intervention, we transfer the patients to the General ward or ICU of the hospital and are removed from the study. The reason for removal is recorded and an off-study document is completed by the study team.Patients who decide to withdraw from the study are defined as “drop-out.”Patients who do not consume at least 80% of ORS offered are considered “non-compliant”.If stool culture reveals an agent that needs antibiotic therapy, the patient is removed from the study, and an off-study document is completed by the study team.All data collected on randomized subjects are kept for intent-to-treat analysis, including patients who withdrew from the study (drop out), have co-morbidity, or are defined as treatment failures or non-compliant.

#### Definitions

Duration of diarrhea in hospital: time in hours, from randomization till resolution of diarrhea.Resolution of diarrhea: the passage of the last liquid or semi-liquid stool before one soft/formed stool or no stool for 12 h [18].Stool output: The weight of stool in g/kg of admission body weight expressed per time period (i.e., per 24 h and for the entire duration of diarrhea).ORS and plain water intakes: The total volume (in ml) of ORS or plain water is taken per kg of admission body weight, expressed per time period.Treatment failure: If diarrhea continues for more than 120 h after enrollment, or requires unscheduled IV fluids due to progressive dehydration, requiring transfer to the general in-patient wardUn-scheduled IV: When intravenous rehydration fluids are given due to the inability of the ORS to maintain hydrationNon-compliance: inability to consume ≥ 80% of ORS

#### Recording of adverse events

All adverse events regardless of the seriousness, severity, or relationship to the study medication are recorded on the adverse events pages of case record forms. Adverse events that meet the definition of a serious adverse event are to be reported on the serious adverse event form provided for this study. Adverse events will be documented in clear, unambiguous medical language. All adverse events not resolved by the end of the study or that have not been resolved upon the subject’s discontinuation in the study will be followed until the event resolves, the event stabilizes, or the event returns to baseline if a baseline value is available. All serious adverse events are to be reported to the secretariat of the Ethics Review Committee of icddr,b within 24h of the investigator or their staff becoming aware of them. Reporting is performed by recording as much information as is available at the time on the serious adverse event (SAE) form by icddr,b IRB.

### Quality assurance

The following measures provide quality assurance:An extensive initial and subsequent ongoing training sessions for study staff in the protocol procedures with a focus on dehydration assessment to ensure the reliability between study staff is high.Real-time electronic data capture in the ClaimIt portal ensures data validation, such as range, logical checks, and data integrity.Good clinical practice (GCP) training and certification are compulsory for all study staff.Study Investigators receive brief weekly progress reports from the data management assistant during the entire study period and participate in regular weekly zoom meetings with donor and CRO. The weekly progress reports include the number of children screened, number of children enrolled, number of treatment failures, number of withdrawn, number of drops out, number of children who completed the study, and number of children currently admitted in the study ward conducted.Study Investigators are responsible for assuring that the training of the study staff is rigorous and of high quality. They schedule the testing and retraining as required. Assessment of individual study personnel’s abilities to use the standardized enrolment criteria and dehydration assessment consistently across the study population are key responsibilities of the study investigators.Entrinsic Bioscience, Obvio, and others identified by them will ensure structured monitoring visits conducted to the study site. The monitoring visits will have as their primary aim quality control and the improvement of study implementation. The monitors will make direct observations of all relevant study procedures and data management activities.The data management assistant runs a weekly set of range and consistency checks, resolves inconsistencies or queries with the sites, and provides data summaries as the trial progresses. The queries are resolved before the next set of weekly check reports.

### Compensation

No financial compensation is provided for participation in the trial.

### Data management

An external data management system (ClaimIt) ensures the harmonization of data collection and data management processes. The study site collects information on a core set of variables with standard definitions. A set of range and consistency checks are applied to these available variables. The study site is responsible for data entry and initial cleaning of the data, including running range and consistency checks, as well as periodic reviews of distributions and identification of outliers. icddr,b resolves any inconsistencies within its database, in consultation with the data collection team, and with verification if needed. The study site is required to provide data on the core set of variables in the ClaimIt database.

### Statistical considerations

#### Sample size and power

The total sample size is 312 male children. In previous non-cholera studies of children comparing an anti-diarrheal to placebo [19–22], the effect sizes for the hourly duration of diarrhea and 24-h stool volume ranged from 0.3 to 1.0 (duration) and 0.3 to 0.7 (stool output), respectively. Outcome improvements ranged from 15 to 45% with treatment (vs. placebo). A clinically significant improvement of 20% produces effect sizes of 0.4 to 0.7 (duration) and 0.3 (stool output) using the pooled standard deviations reported within each outcome. When applied to conventional alpha (0.05) and beta (0.20) values, between 32 and 174 patients per group are required for statistical significance. The maximum anticipated accrual rate of 3 patients per week over 24 months results in 156 patients per group, or 132 patients per group assuming 15% attrition. Therefore, the final anticipated patient group numbers are estimated to provide >99% and 68% power to detect a 20% difference in hourly diarrhea duration and 24-h stool output, respectively.

Justification for the content of the excerpt, based on an independent samples *t*-test (in the Data Analysis part), is reviewed in Table 3. Our sample size estimates were based on detecting a difference in the primary outcome variable (duration of diarrhea). We acknowledge that we were underpowered for secondary outcomes such as stool volume. The secondary outcomes in our study were better classified as exploratory outcomes, which is why we are not adjusting our alpha for multiple endpoints.

**Table 3 Tab3:** Duration of diarrhea (days^a,b^)

Study	M_t_	SD_t_	M_p_	SD_p_	Mdiff	%diff	SDpooled	ES	20%_diff_	ES	nreq	nact	%op
Cojocaru^a^	4.05	1.48	5.73	1.77	1.68	29.3	1.62	1.0	1.14	.71	32	132	99
Santos^b^	4	2.1	4.7	2.2	0.7	14.9	2.15	0.3	0.94	0.44	81	132	99

*Mt* mean of treatment, *SDt* standard deviation of treatment, *Mp* mean of placebo, *SDp* standard deviation of placebo, *Mdiff* mean difference between treatment and placebo, *%diff* percentage of mean difference between treatment and placebo, *SDpooled* pooled standard deviation, *ES* effect size (Mdiff/SDpooled), *20%diff* units for 20% difference from placebo, *ES* effect size (20% units difference/SDpooled), *nreq* sample size required (alpha 0.05, beta 0.20), *nact* actual sample size planned for PR-17028, *%op* percentage observed power (relative to desired minimum of 80%); note – primary study outcome exceeds power criterion

^a^Cojocaru et al. (2002)

^b^Santos et al. (2000)

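### The power above 99% stated for diarrhea duration holds for only one of the two planning studies; for the other (effect size 0.44, 132 per group) it is about 94–95%

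*Protocol article*

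**What the plan says.** The sample-size section of the Protocol article takes a 20% improvement as the clinically relevant effect and turns it into standardized differences: "A clinically significant improvement of 20% produces effect sizes of 0.4 to 0.7 (duration) and 0.3 (stool output"). It then gives the required numbers: "When applied to conventional alpha (0.05) and beta (0.20) values, between 32 and 174 patients per group are required for statistical significance". The planned 156 per group becomes 132 after 15% attrition, and the final numbers are "estimated to provide >99% and 68% power to detect a 20% difference in hourly diarrhea duration and 24-h stool output, respectively". The text describes the calculation as "based on an independent samples *t*-test (in the Data Analysis part), is reviewed in Table 3".

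Table 3 covers duration only and has one row per planning study. The last five entries are the 20% difference in days, its effect size, the required n per group, the planned n per group and the power. The first row ends "1.14 .71 32 132 99" and the second ends "0.94 0.44 81 132 99". The footnote defines the last column as "percentage observed power (relative to desired minimum of 80" percent) and notes that the primary outcome exceeds that criterion.

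**The concern.** The two rows differ only in effect size (0.71 against 0.44), and the planned n is the same. The required n rises from 32 to 81, yet the power is printed as 99 in both. At 132 per group the second study has about 1.6 times the number needed for 80% power (132/81 = 1.63), and that is not enough to bring power to 99%. The text then gives one unqualified power figure for an effect-size range of 0.4 to 0.7.

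Duration is the primary endpoint, so this is the main power statement of the trial. It bears on how a null result would be read: the abstract says that finding no benefit would support leaving current guidance as it is. A reader who takes the power at face value would put the risk of missing a true 20% effect below 1%.

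**Working it through.** **Inputs, all from Sample size and power and Table 3.** Alpha 0.05; independent-samples t-test; n = 132 per group (156 × 0.85 = 132.6); effect sizes 0.71 and 0.44 for duration and 0.3 for stool output. The second effect size is 20% of the placebo mean over the pooled SD: 0.2 × 4.7 = 0.94 and 0.94/2.15 = 0.437, printed as 0.44. Sidedness is not stated and has to be inferred.

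**Formulas (normal approximation, two-sided).**
- Power = Φ(d·√(n/2) − 1.96), with √(132/2) = 8.124.
- Required n per group = 2(1.96 + 0.8416)²/d² = 15.70/d².

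The exact t-test results below use the noncentral t distribution.

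**Step 1: reproduce the plan's other figures.**
- Stool output, d = 0.3: 0.3 × 8.124 − 1.96 = 0.477, Φ = 68.3%; exact t-test 68.0%. Stated: 68%. A one-sided test would give 78.4%, so the plan's calculation is two-sided.
- Required n: 15.70/0.44² = 81.1 (stated 81); 15.70/0.3² = 174.4 (stated 174); at d = 1.14/1.62 = 0.704, 15.70/0.704² = 31.7 (stated 32). These agree.

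**Step 2: apply the same method to duration, 132 per group.**

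| Effect size | Normal approximation | Exact t-test | Stated |
|---|---|---|---|
| 0.71 (first row) | 0.71 × 8.124 − 1.96 = 3.81; >99.9% | >99.9% | 99 |
| 0.44 (second row) | 0.44 × 8.124 − 1.96 = 1.61; 94.7% | 94.5% | 99 |
| 0.437 (second row, unrounded) | 0.437 × 8.124 − 1.96 = 1.59; 94.4% | 94.3% | 99 |

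The first row holds. The second is about 4.5 points too high.

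**Step 3: look for a reading that gives 99% at effect size 0.44 (exact t-test).**

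| Variant | Power at 0.44 | Power at 0.3 (stated 68%) |
|---|---|---|
| One-sided, 132 per group | 97.3% | 78.4% |
| Two-sided, 156 per group | 97.2% | 75.2% |
| One-sided, 156 per group | 98.7% | 84.1% |

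None reaches 99%, and each contradicts the 68% stated in the same sentence. With 132 per group, 99% power needs an effect size of about 0.53. At effect size 0.44 it needs about 191 per group.

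**The case against.** The strongest reply is that nothing in the design depends on the error. The plan's criterion is 80% power; 94–95% clears it easily, and the footnote's conclusion that the primary outcome exceeds the criterion remains true. The test, alpha and enrolment target are unaffected, and a null result at 94–95% power is still informative. All of this stands and limits the weight of the point. It does not make the printed figure correct.

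A reader might infer more than the document supports:

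- **Power could be as low as 90%.** Taken literally, an effect size of 0.40 gives 89.9%. But the text's range of 0.4 to 0.7 appears to be Table 3's 0.44 and 0.71 rounded to one decimal, and no planning row has 0.40. It is not a separate planning case.
- **The required n of 81 is also wrong.** The exact t-test gives 82 to 83, but the normal approximation gives 81.1 and matches the plan's other required numbers. This is a choice of method.
- **The 120 h limit on follow-up lowers the power further.** That may be so, but any figure depends on the shape of the duration distribution, on the SD under treatment and on how children unresolved at 120 h are scored. The sample-size section fixes none of these, and the Statistical analysis section also plans life-table, log-rank and Cox analyses.
- **The planning durations may run from onset rather than from randomization.** The document does not say, and the planning studies are not at hand.
- **The favourable study was picked as the headline.** Table 3 shows both studies and prints 99 for each. A wrong table entry carried into the text explains this equally well.

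**Conclusion.** The point holds as an arithmetic error in a stated property of the primary endpoint. The power for the second planning study is 94.5% at effect size 0.44 (94.3% unrounded), not 99%, so the single figure in the text is true only under the first study's assumptions. The type II error at the second study's effect size is about 5.5–5.7%, more than five times the level implied by the text.

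This rests on the plan's own alpha, test, effect sizes and 132 per group. Two-sidedness is inferred from the 68% and the required numbers, but the conclusion does not depend on it, since a one-sided test also falls short of 99%. It would be wrong to infer that the trial is underpowered for duration: on the plan's assumptions both studies give power well above 80%, and 312 children remain sufficient.

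**What to change.** In Table 3, change the power entry in the second row from 99 to about 94–95. In the text, replace the single duration figure with a range tied to its inputs: about 94% (effect size 0.44) to above 99% (effect size 0.71), with 132 per group and a two-sided alpha of 0.05. Leave the required n of 81 as it is.

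The cost is one table cell and one sentence. Enrolment, the analysis and the alpha level do not change; the stated power only becomes slightly less favourable.

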#### Statistical analysis

Data are collected on paper and entered electronically capturing information such as demographics, medical history, clinical assessments, clinical course, etc., and transcribed into an electronic database using Statistical Package for Social Sciences (SPSS) (version 20), STATA, or equivalent. The primary analysis will be intended to treat analysis which will include all of the patients who were randomized in the study. A per-protocol analysis will also be done only including only those randomized subjects with efficacy data on diarrhea volume and who have taken at least 80% of the investigational product. If the distribution of the variable does not have a normal distribution, a log transformation of data will be performed before the t-test analysis or a non-parametric equivalent test will be performed. Differences between the two treatment groups (VS002A versus WHO ORS) will be examined for baseline characteristics before performing a statistical analysis of the efficacy endpoints. If any differences are considered to be clinically important, subgroup analysis will be presented for the relevant endpoints. Depending upon the normality of distribution of the quantitative variables, a *t*-test or Mann-Whitney *U* test will be used to compare the duration of diarrhea, stool output, the output of vomit, and ORS intake. The chi-squared test will be used to compare treatment failures, unscheduled IV, and frequency of vomiting. Comparison of the primary outcome will be performed with and without adjustment of design effects (age stratum) and patient characteristics (cause, clinical characteristics on admission, nutritional status). All analyses will be performed separately on children as per protocol and on all children on an intention-to-treat basis. In addition, a life-table analysis will also be performed. Time to cessation of diarrhea will be compared by log-rank test, and adjustments of covariates will be made via Cox proportional hazards regression.

An interim data analysis will be performed by a third-party biostatistician once 50% of the enrollment has been completed. The interim analysis will not unblind or regroup the study population; the assessment will be done in the whole patient cohort. The analysis will include safety and adverse events, tolerability and compliance to the ORS intake, and the severity of diarrhea/duration of diarrhea after randomization (to assess the severity of the disease and determine if sample size assumptions are correct). No efficacy calculations will be performed and no comparison between groups will be done.

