#### Treatment procedures

The study patients are placed on diarrhea cots. Initial treatment dosing with WHO-ORS or VS002A is estimated using bodyweight following 5–10 ml/kg after each loose stool as per icddr,b guideline, to maintain the ongoing loss. Adjustments may be required and hydration is maintained using smaller or larger volumes depending on measured losses. Children are fed using a spoon. Assessment and treatment are to continue until the resolution of diarrhea. The child is supplemented with tablet zinc: one tablet (20 mg) per day for 10–14 days [2].

In young children who cannot control micturation, a pediatric urine collection (PUC) bag is applied to facilitate the separate collection of stool and urine.

The patient receives liquid, semi-solid, and solid foods appropriate for age. Breast-fed children continue to receive breast milk. If stool culture reveals any pathogen, then the patients receive an appropriate antibiotic if applicable and are excluded from the study (e.g., azithromycin in cholera). Intakes of ORS, food, and medicines are supervised by a nurse and are recorded. Vital signs are recorded for each patient every 4 h. Intake of ORS and water is recorded every 4 h while outputs of stool and urine and vomitus, and stool frequency are recorded continuously. Clinical assessment of the study children is performed by the study investigators and/or designated research physicians. Vital signs and body weight are measured and recorded by experienced nurses of the Study Ward. And other measurements, e.g., stool frequency and volume/weight, intake of rehydration fluids, and urine outputs are measured by designated health workers under the supervision of the study nurse who would record them. Each participating child is closely monitored for the occurrence of any adverse events such as worsening diarrhea or increased vomiting, and their severity and duration are noted and information is also recorded for analysis.

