### Outcomes

#### Primary outcomes

Duration of diarrhea in hospital (hours)

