#### Exploratory outcomes

Stool output in the 1st 24 h of hospitalization (g/kg body wt.), further divided into two 12-h periodsTotal stool output during hospitalization (g/kg body wt.)ORS intake in the 1st 24 h of hospitalization (g/kg body wt.)Total ORS intake (ml/kg body wt.)Unscheduled IV (frequency/ORS group)Treatment failure (frequency/ORS group)Output and frequency of vomitingChange in body weight (between pre-randomization and post-treatment)Urine output in the 1st 24 h of hospitalization (g/kg body wt.)Total urine output during hospitalization (g/kg body wt.)Documented infectious agentBlood chemistry (between pre-randomization and after 24 h of treatment)Gut health biomarker: citrulline (CIT) and kynurenine to tryptophan ratio (KT) between pre-randomization and at 24 hours after the enrolment)

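### The one per-protocol set is defined by having stool-volume data, an exploratory outcome, yet it is also used for the primary endpoint of duration

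*Protocol article*

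**What the plan says.** The Definitions section fixes the primary endpoint: "Duration of diarrhea in hospital: time in hours, from randomization till resolution of diarrhea". Resolution is judged there from the consistency and timing of stools. The Exploratory outcomes section lists stool output by weight, beginning with "Stool output in the 1st 24 h of hospitalization (g/kg body wt".), and the Sample size and power section concedes that the trial is underpowered for stool volume.

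The Statistical analysis section makes intention to treat primary: "The primary analysis will be intended to treat analysis which will include all of the patients who were randomized in the study". It adds a per-protocol analysis "only including only those randomized subjects with efficacy data on diarrhea volume and who have taken at least 80% of the investigational product". Later in the same section: "All analyses will be performed separately on children as per protocol and on all children on an intention-to-treat basis". No other per-protocol definition appears in the article, and the rule does not mention duration data.

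On adherence, the section on criteria for removal says: "Patients who do not consume at least 80% of ORS offered are considered" non-compliant.

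**The concern.** A per-protocol analysis should show what happens among children who took the product as intended. Here entry has a second condition: having data on an outcome that is not the one being analysed. For the stool-output analyses that condition is natural. For duration it is irrelevant, and it can only remove children whose primary outcome is known.

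What is at stake is interpretation. If the per-protocol and intention-to-treat durations differ, the reader will want to attribute the difference to adherence. With this rule, part of it could come from the availability of stool-volume data.

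**Working it through.** **Step 1. Match the rule to the endpoints.** Duration (Definitions) needs the time of randomization and the time of the last liquid or semi-liquid stool. Stool output (Definitions) needs stool weights. The per-protocol rule (Statistical analysis) asks for the second kind of data and then governs analyses of the first.

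**Step 2. Follow each kind of adherent child through the rule as written.**

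| Stool-volume data | Resolution time | In the per-protocol set? | Effect on the duration analysis |
|---|---|---|---|
| Yes | Observed | Yes | None |
| None usable | Observed | No | A valid duration is lost |
| Yes | Not observed | Yes | No observed duration for a t-test or Mann-Whitney test; can be censored in the log-rank and Cox analyses |
| None usable | Not observed | No | No observed duration is lost |

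The second row is the material one. It can occur: a usable weight needs stool kept apart from urine, and the protocol treats that as a practical difficulty, since it enrolls only boys for this reason (Study setting and population) and uses urine bags (Treatment procedures). A collection can be spoiled while the time and consistency of the stool are still known. The article does not say how often.

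**Step 3. Size, as loss of power.** Inputs from Sample size and power and its Table 3: 132 per group after 15% attrition (156 × 0.85 = 132.6), alpha 0.05 (taken as two-sided), and a 20% difference of 0.94 days with pooled SD 2.15, so d = 0.94/2.15 = 0.437. This is the less favourable row of the table. The text gives 0.4 as the lower end of the range.

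The plan's own figures first, by two-sample t-test:
- Stool output, d = 0.3, n = 132: power 68.0%, against 68% stated.
- Duration, first row of Table 3, d = 1.14/1.62 = 0.704, n = 132: power 99.99%, consistent with the stated figure of more than 99%.
- Duration, second row, d = 0.437, n = 132: power 94.3%, against 99 in the table. That is a separate matter and this point does not depend on it; 94.3% is the baseline below.

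As a check, the normal approximation is power = Φ(d√(n/2) − 1.96). With d = 0.437 and n = 132 it gives Φ(3.55 − 1.96) = Φ(1.59) = 94.4%.

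The share of children without usable volume data is not given. Assuming 5%, 10% or 15%:

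| Loss (assumed) | n per group | Power, d = 0.437 | Power, d = 0.40 |
|---|---|---|---|
| 0% | 132 | 94.3% | 89.9% |
| 5% | 125 | 93.1% | 88.3% |
| 10% | 119 | 91.9% | 86.7% |
| 15% | 112 | 90.3% | 84.6% |

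The n for 80% power is about 84 per group at d = 0.437 and 100 at d = 0.40. So about 132 − 84 = 48, or 132 − 100 = 32, children per group could be lost before power fell below 80%. Because 132 is already net of attrition, some of the assumed loss may be counted twice, so the table leans pessimistic. Precision is not the issue; clean interpretation is.

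**The case against.** The strongest reply is that the mismatch may be almost empty in practice. Children lie on diarrhea cots, and stool output and stool frequency are both recorded continuously under a study nurse's supervision, so a child with no stool-volume record would often lack a reliable duration too. The analysis is supportive in a superiority trial whose primary analysis covers all randomized children. And this is a condensed article; a fuller plan may refine the set. The first two arguments stand and limit the size of the point. The third does not remove it, because the article does not leave the rule open: it states one, and that rule fits the wrong endpoint.

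A reader might infer more than the article supports:

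- *That any child with incomplete stool weights is excluded.* The rule asks for volume data, not complete volume data. Read literally, a child with some weights stays in.
- *That the rule selects on outcome, because weights go missing in long or heavy diarrhea.* Nothing in the article says so. A child with longer diarrhea also has more chances to contribute some volume data.
- *That children without a resolution time are wrongly kept.* They bring no observed duration to a t-test or Mann-Whitney test, and censoring them in the time-to-event analysis is appropriate.
- *That the 80% rule has two denominators, ORS offered and investigational product.* The investigational product is the ORS, and the most natural reading is one rule worded in two ways. Since the initial volume is set at "5–10 ml/kg after each loose stool" and may then be adjusted, there is no fixed total, so using the same words in both places would help. It is a wording point only.

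**Conclusion.** The point holds as a definition error in a supportive analysis. The single per-protocol set is keyed to an exploratory outcome and applied to the primary one, so an adherent child with a valid duration can be left out for a reason unrelated to adherence or to duration. The article does not show that any child is in fact misplaced, or in which direction an estimate would move. The number is probably small. Under an assumed loss of 5% to 15%, the power cost is about 1 to 4 percentage points at d = 0.437 and about 2 to 5 at d = 0.40. The intention-to-treat primary analysis is untouched. It should be corrected because the correction is nearly free, not because the trial's conclusion depends on it.

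**What to change.** Define the per-protocol set by adherence alone: randomized children who took at least 80% of the ORS offered, in the wording of the section on criteria for removal. Then judge data availability endpoint by endpoint, and require stool-volume data only for the stool-output analyses.

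For duration, include every adherent child with follow-up for resolution. Keep treatment failures, whether unresolved at 120 h or transferred for unscheduled IV fluids, and children removed before resolution, and handle them by the same rule as in the intention-to-treat time-to-event analysis. Limiting the set to children with an observed resolution or still unresolved at 120 h would not do: it could drop those who fail earlier through unscheduled IV fluids, which would itself select on outcome.

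The cost is a few sentences and no new data. The Blinding section places final unblinding after the statistical analysis, so the change can be made while treatment groups are still masked.
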